### Phase 2: Machine Learning Model Implementation and Evaluation

Music recommendation is an active area of research within the information retrieval community, with researchers facing unique challenges, such as data sparsity, complexity in evaluation, and personalization for cultural and situational awareness. The cold start problem, a lack of historical information for making decisions about new users or items, is a common issue across many recommendation systems that persists in the music domain [36,37]. Recent work has found promising results by using neural network models and incorporating metadata features such as song artist or genre with user interaction data to form a collaborative knowledge graph [37,38]. In particular, users, songs, and metadata categories are treated as nodes in a graph. Connecting edges represent semantic meaning, like a song belonging to a genre or a user favoriting a song. Neural network–based approaches like DeepWalk can be used for learning latent representations of the graph’s nodes in vector space [37,39]. At recommendation time, a song is compared to others in vector space, returning the most similar songs to the end user. This approach will allow the system to make recommendations based on the preferences of similar users in conjunction with shared music metadata and clinical features to maximize the relevance of recommendations.

The modeling architecture will largely follow Bertram et al [37] for creating knowledge graph embeddings of songs and relevant metadata features of both users and songs. Authors LD and VP will conduct explorations to vary the metadata features included in the knowledge graph and tune hyperparameters of the DeepWalk model. This will allow for thorough exploration of feature selection and model architecture choices, with the best performing modeling pipeline deployed for user testing. Models and data processing will be implemented in Python (Python Software Foundation) with widely used ML libraries, *scikit-learn* and *pytorch*, and support for graph structures with *pytorch-geometric* and *networkx*. The algorithms will be developed in collaboration with the data core at the University of Massachusetts Center for Data Science and the Massachusetts AI and Technology Center.

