The data will be split into training, validation, and testing sets by user using 5-fold cross-validation. This will balance training and evaluation variances and allow for more efficient use of the relatively sparse data compared to using a single data split for training, validation, and testing sets. Splitting data at the user-level will simulate the cold start problem in our experiments. The model with the best average performance across the 3 test sets will be retrained on the entire dataset, a standard practice in ML. Baseline performance will be measured using a purely random recommendation system and a content-based learning-to-rank approach that relies solely on metadata features. These baseline benchmarks will help gauge the added benefit of more complex neural network recommendation algorithms.

Because clinical features may be in tension with musical preferences or musical features, multiple metrics are needed in order to understand the trade-off being made by the recommendation algorithm. The metrics that will be used to evaluate performance are root mean square error, normalized discounted cumulative gain, and a user-reported satisfaction score [36]. Root mean square error will be used to evaluate the error between the recommendation system’s estimated satisfaction score and the user’s true satisfaction score to ensure that it can accurately predict the user’s label of the song. Normalized discounted cumulative gain, a ranking quality metric, will be used on the songs recommended by the system to ensure that the test data songs are being recommended in an order equivalent to their user-preferred ranking. As part of further testing, a sample of users will be given a set of playlists recommended by the system and asked to answer the survey questions from phase 1. By comparing the satisfaction scores across phases, a comparison can be made as to the direct effects on the listener of the songs recommended.

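### RMSE is one of three performance metrics, but the two named baselines do not assure it a meaningful benchmark, and no mean-rating predictor is named

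*Protocol article*

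**What the plan says.** All the relevant text is in the protocol article, Methods, under Phase 2: Machine Learning Model Implementation and Evaluation.

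- Metrics: "The metrics that will be used to evaluate performance are root mean square error, normalized discounted cumulative gain, and a user-reported satisfaction score". None of the three is ranked above the others.
- What RMSE measures: "Root mean square error will be used to evaluate the error between the recommendation system’s estimated satisfaction score and the user’s true satisfaction score".
- Comparators: "Baseline performance will be measured using a purely random recommendation system and a content-based learning-to-rank approach that relies solely on metadata features".
- Their purpose: "These baseline benchmarks will help gauge the added benefit of more complex neural network recommendation algorithms". The text does not say on which metric or metrics the baselines will be compared.
- Model output, in the general description of the method: "At recommendation time, a song is compared to others in vector space, returning the most similar songs to the end user".

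Data are split by user, so that test users are new to the model. The Measures section says that song questions are answered on 5-point Likert scales.

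**The concern.** RMSE needs a number on the rating scale for each user and song. NDCG needs only an ordering. The baselines chosen to show what the neural model adds suit the second metric better than the first. A purely random recommender has no natural RMSE. Many learning-to-rank models give scores that order songs but do not sit on a 1 to 5 scale.

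The usual reference for RMSE is a predictor that knows only averages: one overall mean, or one mean per song. Neither is named. Without them, a reported RMSE cannot be separated into three parts: learning the general level of the ratings, learning which songs are liked on average, and learning what suits a particular kind of user. Only the third is personalisation, and personalisation is what the study sets out to deliver. If the gap were filled by random ratings, the comparison would favour almost any model.

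**Working it through.** The article states no RMSE, RMSE target or baseline RMSE, so there is no figure to reproduce. The check sets out what each named comparator yields, and then how weak a random-rating benchmark would be.

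**1. What each comparator yields**

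| Comparator | Predicted rating? | Usable for NDCG? |
|---|---|---|
| Purely random recommender (named) | No | Yes |
| Metadata-only learning-to-rank (named) | Only if pointwise; type not stated | Yes |
| Global mean or song mean (not named) | Yes | Song mean yes; global mean ranks nothing |

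**2. Inputs**

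- Scale 1 to 5 (Measures section).
- Mean rating 3.5 to 4.0: assumed.
- SD 1.0 to 1.2: assumed. The article gives an SD of 1.2 for the aim 3 mean acceptability score. Using it for single song ratings is an assumption.

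**3. Formulas**

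- Constant at the mean: RMSE = SD (ignoring the small error in estimating the mean).
- Uniform random integer from 1 to 5, which has mean 3 and variance (25 − 1)/12 = 2, independent of the rating: RMSE = √(2 + SD² + (mean − 3)²).
- Random draw from the rating distribution itself: RMSE = SD × √2.

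**4. Results**

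| Mean | SD | Constant | Uniform random | Apparent reduction |
|---|---|---|---|---|
| 3.5 | 1.0 | 1.00 | √3.25 = 1.80 | 45% |
| 3.5 | 1.2 | 1.20 | √3.69 = 1.92 | 38% |
| 4.0 | 1.0 | 1.00 | √4.00 = 2.00 | 50% |
| 4.0 | 1.2 | 1.20 | √4.44 = 2.11 | 43% |

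The reduction is 1 − constant/uniform. A random draw from the true rating distribution is the kinder version. It gives 1.41 (SD 1.0) to 1.70 (SD 1.2), and the constant still shows a reduction of 1 − 1/√2 = 29%.

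**5. Wider range**

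For SD 0.8 to 1.4 and means 3.0 to 4.25, the constant gives 0.80 to 1.40, the random draw 1.13 to 1.98, and the uniform rating 1.62 to 2.35. At any given mean and SD the constant is always the lowest.

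**6. Models that do carry information**

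Let r be the correlation of the model's score with the rating, and take SD 1.2.

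- Score calibrated to the rating scale: RMSE = SD × √(1 − r²). At r = 0.3 this is 1.145, and it is never worse than the constant's 1.20.
- Uncalibrated score that has the same mean and SD as the ratings: RMSE = SD × √(2 − 2r). At r = 0.3 this is 1.42. It is worse than the constant until r exceeds 0.5.

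Whether an informative model beats a constant therefore depends on calibration, which the article does not describe.

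**The case against.** The strongest reply is that the article never says the baselines are compared on RMSE. The baselines are introduced before the metrics and are not tied to any of them. RMSE has its own stated purpose, a check that the system predicts the user's label, and NDCG can score both baselines directly. This stands. It rules out saying that the plan specifies an impossible comparison. It does not supply an RMSE benchmark, and nothing in the text limits the added-benefit comparison to NDCG.

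A reader might go further and infer four things that the document does not support.

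- *That the main model cannot have an RMSE because it returns only similar songs.* The article says that the system has an estimated satisfaction score. How that score is derived is a detail that an article may leave to the full protocol. Leaving it out is not an error.
- *That neither baseline can predict a rating.* A pointwise learning-to-rank model can regress the rating directly, and the type is left open.
- *That the models would lose to a constant.* This is shown only for random ratings and for weakly correlated, uncalibrated scores. It is not shown for the embedding model or for the metadata baseline.
- *That the conclusion of aim 2 would be wrong.* Aim 2 states no test of RMSE superiority over random. NDCG, the metadata baseline and user-reported satisfaction in a separate sample also bear on it.

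It is also fair to say that the 38% to 50% describes a procedure nobody has proposed. It shows how weak the benchmark would be if the gap were filled that way. It does not predict the study's result.

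**Conclusion.** The point holds in a limited form. RMSE is a stated performance metric, and the comparators named for judging the neural model's added benefit do not assure it a meaningful reference. The random recommender gives no rating, the learning-to-rank model may or may not give one, and no mean-rating predictor is named.

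The size of the problem depends on how the gap is filled. With random ratings, a constant would show an apparent 29% (random draw) to 50% (uniform, mean 4.0, SD 1.0) lower RMSE, under an assumed mean of 3.5 to 4.0 and SD of 1.0 to 1.2. If the learning-to-rank model is pointwise, there is one usable RMSE comparator. Even then, the comparison would not show whether the neural model improves on average song ratings.

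This is an inexpensive improvement worth making before results are reported. It is not a contradiction that invalidates the evaluation.

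**What to change.** - Add two RMSE benchmarks, both fitted in the training folds and evaluated on the held-out users: the global mean rating and the mean rating of each song. Both can be computed for users the model has not seen, so they fit the user-level split. Where a song has no training ratings, fall back to the global mean.
- State whether the learning-to-rank baseline predicts ratings. If it does not, add a metadata-only regression of the rating for RMSE.
- Use the random recommender for NDCG only, and say so.
- Interpret an RMSE gain as added benefit of the neural model only relative to the song-mean predictor.

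Cost: a few lines of analysis code on data already collected, and possibly a smaller reported gain. The Limitations section accepts that 1000 participants is a small sample for training this kind of model, so failing to beat the song mean is a real possibility and should be visible if it happens.

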**Methods:**

Participants (N=1200) will be aged 55 years or older and residing in the United States. In phase 1, participants (n=1000) will receive 5 randomized songs and complete a survey to understand the sentiment, cultural relevance, and perceived benefit for each song. Brief, researcher-created Likert surveys will be used. In phase 2, survey data will be used to develop ML algorithms in collaboration with the University of Massachusetts Amherst Center for Data Science and Artificial Intelligence. These ML models will be integrated into the digital music intervention and tested with a separate sample of 200 participants. Similar to phase 1, participants will be provided with sets of songs generated by the recommendation system based on the target goal (ie, to reduce depression). The recommendation accuracy of the ML algorithm will be assessed using multiple performance metrics, including root-mean-square error and normalized discounted cumulative gain as well as the mean acceptability score with a goal of 85% user acceptability.

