For Aim 3, the goal is to develop a ML model with ≥80% accuracy in creating individualized therapeutic music playlists and achieve a user acceptability score of 85% or higher among rural-residing older adult users. Using the same survey questions from phase 1 (see Multimedia Appendix 1), the user acceptability score will be based on the average ratings for questions regarding the overall preference, relevance, and perceived benefit of the playlists. An a priori power analysis was conducted using G*Power version 3.1 [40] to determine the required sample size for a 1-sample *t* test for aim 3. The goal of the analysis was to detect a mean acceptability score significantly greater than 4.25 (indicating 85% acceptability), with a margin of error of 0.2 and an estimated SD of 1.2. Assuming a medium effect size (d=0.30), an α level of .05, and a desired power of 0.80, the analysis revealed that a minimum of 139 participants would be needed to ensure adequate statistical power.

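### The Aim 3 minimum of 139 does not follow from the stated power inputs (d=0.30, α .05, power 0.80), which give 71 or 90; it matches a 95% confidence-interval width calculation instead

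*Protocol article*

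**What the plan says.** All the relevant text is in the protocol article, in the last paragraph of the section Phase 2: Machine Learning Model Implementation and Evaluation, apart from the planned sample size.

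- The calculation was made "to determine the required sample size for a 1-sample *t* test for aim 3".
- The score under test is defined as follows: "the user acceptability score will be based on the average ratings for questions regarding the overall preference, relevance, and perceived benefit of the playlists".
- The aim of the test is to "detect a mean acceptability score significantly greater than 4.25 (indicating 85% acceptability"). The wording is directional, but the text does not say whether the test is one- or two-sided.
- The inputs are given "with a margin of error of 0.2 and an estimated SD of 1.2", followed by d=0.30, α .05 and power 0.80.
- The result is that "the analysis revealed that a minimum of 139 participants would be needed to ensure adequate statistical power".
- The Abstract, under Methods, says that the models will be "tested with a separate sample of 200 participants".

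**The concern.** The inputs and the output of the power analysis are printed together, so the result can be checked directly, and it fails the check. The paragraph also mixes two kinds of sample-size reasoning. A margin of error belongs to a precision calculation. An effect size and a power belong to a test. The text gives one of each and does not say how they relate, in particular whether 0.2 is only the width wanted for the interval or also the smallest excess over 4.25 that matters.

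This is the only power statement in the document, and it supports the only hypothesis test that the document names. As written, a reader cannot tell which difference the study was sized to detect, and the claim of 80% power at 139 is not correct for the stated effect. That affects how a non-significant Aim 3 result should be read: as evidence against the recommender, or as a test with limited power for a small excess over the target.

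**Working it through.** **Inputs (Phase 2 section, Aim 3 paragraph; n=200 from the Abstract).** Null mean 4.25; α = .05; power = 0.80; d = 0.30; SD = 1.2; margin of error = 0.2; stated minimum 139; planned sample 200. Sidedness is not stated, so both versions are shown.

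**1. Trying to reproduce 139 from the stated power inputs.** The normal approximation is n = ((z_α + z_power)/d)².

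- One-sided: ((1.645 + 0.842)/0.30)² ≈ 68.7, so 69. The exact noncentral t calculation gives **71**.
- Two-sided: ((1.960 + 0.842)/0.30)² ≈ 87.2, so 88. The exact calculation gives **90**.

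Neither is 139. Exact power at n = 139 for d = 0.30 is 97.0% one-sided and 94.0% two-sided.

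**2. The precision formula with the paragraph's own figures.** n = (z × SD/margin)² = (1.96 × 1.2/0.2)² = 11.76² = 138.3, rounded up to **139**. This matches exactly and contains neither d nor power. With a t quantile in place of 1.96 the answer is 141, so the match is to the usual z formula. Getting exactly 139 from a one-sample t power calculation takes inputs that are not in the text, such as d = 0.24 two-sided at 80% power or d = 0.25 one-sided at 90%.

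**3. How the two inputs relate.** If 0.2 were the difference to detect, d = 0.2/1.2 = 0.167. If d = 0.30 is the target at SD 1.2, the raw difference is 0.30 × 1.2 = 0.36, that is, a true mean of 4.61. These are different targets.

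**4. Power under each reading (exact noncentral t, α .05).**

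| Target | n for 80% (one-/two-sided) | Power at 139 | Power at 200 |
|---|---|---|---|
| d = 0.30 | 71 / 90 | 97.0% / 94.0% | 99.5% / 98.8% |
| 0.2 at SD 1.2 (d = 0.167) | 224 / 285 | 62.2% / 49.7% | 75.9% / 65.0% |

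**5. What n = 200 delivers at SD 1.2.**

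- 95% half-width: 1.96 × 1.2/√200 = 0.166, about 0.17. (At n = 139: 1.96 × 1.2/√139 = 0.199.)
- The standardised difference detectable with 80% power is 0.1764 one-sided and 0.1991 two-sided. Multiplied by 1.2 these are 0.212 and 0.239, so the true mean must be at least about 4.46 or 4.49.

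**6. Sensitivity to the SD.** The tested quantity is an average of ratings within a person, so its SD may be below 1.2. The range here is an assumption. For a difference of 0.2 at n = 200:

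- SD 1.0 (d = 0.2/1.0 = 0.20): 88% one-sided, 80% two-sided.
- SD 0.8 (d = 0.2/0.8 = 0.25): 97% one-sided, 94% two-sided.

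**The case against.** The strongest reply is that no harm follows. The only effect size the article states is d = 0.30; it calls 0.2 a margin of error and never a difference to detect. At d = 0.30 the planned 200 gives about 99% power, and 200 also exceeds 139. Recruitment for both phases was complete by June 2025, so no decision on sample size remains. All of this stands. It limits the consequence, but does not make 139 the output of the stated analysis.

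Some stronger readings are tempting and are not supported:

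- **That Aim 3 is underpowered, little better than a coin flip.** The 50% figure needs three conditions together: 0.2 as the target difference, a person-level SD of 1.2, and a two-sided test at n = 139. The document fixes none of the three, and it plans 200. With a smaller SD, which is plausible for an averaged score, 200 reaches 80% or more even for a difference of 0.2.
- **That an SD of 1.2 is impossible at a mean of 4.61.** On a 1–5 scale the largest possible SD there is √(0.39 × 3.61) = 1.187. That rounds to 1.2, and the SD is an estimate given to one decimal. It would be an extreme distribution, but it is not excluded at the stated precision.
- **That the person-level SD can be worked out from the number of ratings averaged.** The article does not fix how many ratings enter the score, so no particular value follows.
- **That the confidence-interval origin of 139 is established.** The document reports a G*Power analysis. The exact match is strong evidence, but still an inference.

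**Conclusion.** The statement is wrong as written. A one-sample t test with d = 0.30, α .05 and power 0.80 needs 71 (one-sided) or 90 (two-sided) participants, and 139 gives 97% or 94% power for that effect. This conclusion uses only the printed inputs and does not depend on how 139 arose. The most likely explanation is a precision calculation reported as a power calculation.

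The practical weight depends on an intention that the text does not state. If d = 0.30 is meant, the fault is a misdescribed justification and the planned 200 is ample. If 0.2 is the difference of interest and the SD of the per-person score really is 1.2, the planned 200 falls short of 80% (76% one-sided, 65% two-sided). The document does not support asserting the second reading over the first. It does need to say which one applies.

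**What to change.** Rewrite the Aim 3 sample-size statement, with no change in enrolment:

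1. Either present 139 as a precision-based size (95% confidence-interval half-width 0.20 at SD 1.2), or replace it with 71 one-sided / 90 two-sided as the size for d = 0.30 at 80% power.
2. State the sidedness of the test and a single target difference from 4.25, and say whether 0.2 is only a precision margin.
3. State what the planned 200 delivers at the assumed SD of 1.2: half-width about 0.17, and 80% power if the true mean is at least about 4.46 (one-sided) or 4.49 (two-sided).
4. Say that these figures depend on the SD of the averaged per-person score, which may be below 1.2, and show them over a range of SDs. Phase 1 data can guide that range but should not fix it: Phase 1 songs were randomly chosen, whereas Aim 3 scores recommended songs against a target near the top of the scale.

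The cost is one reworded paragraph and a short recalculation. The article describes analysis as still underway, so the clarification can be made before the Aim 3 result is interpreted. If 0.2 at SD 1.2 turns out to be the intended target, the reported power becomes less favourable than the current text claims.

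### The Aim 3 minimum of 139 does not follow from the one-sample t test described, whose inputs give 90 (two-sided) or 71 (one-sided), and the passage names two incompatible target differences

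*Protocol article*

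**What the plan says.** The calculation is in the protocol article, Methods, Phase 2: Machine Learning Model Implementation and Evaluation, in the paragraph on Aim 3. The software is G*Power 3.1, used "to determine the required sample size for a 1-sample *t* test for aim 3". The stated purpose is to "detect a mean acceptability score significantly greater than 4.25 (indicating 85% acceptability"). To this the passage adds a precision target and a spread: "with a margin of error of 0.2 and an estimated SD of 1.2". The remaining inputs are given as "Assuming a medium effect size (d=0.30), an α level of .05, and a desired power of 0.80". The conclusion drawn is: "the analysis revealed that a minimum of 139 participants would be needed to ensure adequate statistical power".

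The passage does not say whether the test is one- or two-sided, and gives no allowance for dropout or multiplicity. The Abstract (Methods) sets the separate Aim 3 sample at 200.

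**The concern.** The passage states the test, effect size, alpha and power, so the result can be checked directly. It fails the check: 139 is well above what these inputs require.

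The inputs also conflict. A margin of error does not enter a power calculation for a one-sample t test. Taken as the difference to detect, 0.2 points at SD 1.2 is an effect little more than half of d=0.30. The reader cannot tell which excess over 4.25 the study was sized to detect.

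This is the only quantitative sample-size justification in the article. The 1000 participants for Aims 1 and 2 were set by deliberation with data consultants (Phase 1: Data Collection and Preprocessing). Whether 200 reach the stated 80% power depends on which difference was meant.

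**Working it through.** **Inputs** (Aim 3 paragraph, except the last): one-sample t test; null mean 4.25, directional wording; d=0.30; alpha .05; power 0.80; margin of error 0.2; SD 1.2; stated minimum 139. Planned sample 200 (Abstract).

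**Step 1: try to reproduce 139 from the stated inputs.** The normal approximation is n = ((z_alpha + z_beta)/d)².
- One-sided: ((1.645 + 0.842)/0.30)² ≈ 68.7, so 69.
- Two-sided: ((1.960 + 0.842)/0.30)² ≈ 87.2, so 88.

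The exact calculation uses the noncentral t distribution with n−1 degrees of freedom and noncentrality d√n.
- One-sided: 70.07, so 71.
- Two-sided: 89.15, so 90.

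The stated 139 is 139/90 = 1.54 times the two-sided figure and 139/71 = 1.96 times the one-sided figure. Rounding cannot explain it.

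**Step 2: try other settings of the one-sample test at d=0.30.**

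| Alpha | Power | n two-sided | n one-sided |
|---|---|---|---|
| .05 | 0.80 | 90 | 71 |
| .05 | 0.90 | 119 | 97 |
| .05 | 0.95 | 147 | 122 |
| .01 | 0.80 | 134 | 115 |

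None gives 139. The closest found, two-sided alpha .025 with 90% power, needs 141 and departs from both the stated alpha and the stated power.

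**Step 3: calculations that do give 139.**
- *Precision.* For a 95% confidence interval with half-width 0.2: (1.96 × 1.2/0.2)² = 11.76² = 138.3, so 139. This uses the passage's margin and SD but neither d nor power. With t quantiles instead of 1.96 it gives 141.
- *Two-sample t test.* One-sided with d=0.30, alpha .05 and power 0.80, the exact size is 138.07, so 139 per group. This uses the passage's d, alpha and power but the wrong test.
- *Unstated dropout.* Inflating 90 for 35% loss: 90/0.65 = 138.5, so 139. The passage mentions no such allowance.

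The first two match equally well, and the article does not decide between them.

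**Step 4: the two targets.** d=0.30 is 0.30 × 1.2 = 0.36 points, a mean of 4.61. A difference of 0.2 points is d = 0.2/1.2 = 0.167, a mean of 4.45.

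| Difference | n for 80% power (two-sided / one-sided) | Power at 139 | Power at 200 |
|---|---|---|---|
| d=0.30 (0.36 points) | 90 / 71 | 0.940 / 0.970 | 0.988 / 0.995 |
| d=0.167 (0.2 points) | 285 / 224 | 0.497 / 0.622 | 0.650 / 0.759 |

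**Step 5: what the samples can do.**
- Smallest effect detectable with 80% power at n=139: d=0.239 two-sided, 0.212 one-sided.
- At n=200: d=0.199 two-sided, 0.176 one-sided.
- 95% half-width at n=200 and SD 1.2: 1.96 × 1.2/√200 = 0.166, about 0.17 points.

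**The case against.** The strongest defence is that little depends on the number. At the only declared effect size, 139 secures more than the 80% promised, and the planned 200 exceed 71, 90 and 139 alike. The surveys were complete by June 2025 (Results), so enrolment cannot be affected. The study is a pilot, and the t test sits beside other Aim 3 measures: ranking quality, prediction error and an accuracy goal. All of this stands and limits the severity. It does not make 139 the output or the minimum of the analysis described.

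A reader might infer from the exact match that 139 is a confidence-interval calculation mislabelled as a power analysis. The article does not support that as a fact. Choosing the two-sample family in G*Power with the stated d, alpha and power gives the same 139 per group. Declaring 139 a precision figure could write into the protocol a rationale that was never used.

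A reader might also infer that Aim 3 is underpowered. That does not follow either. The article calls 0.2 a margin of error, and its declared effect size is d=0.30. The shortfall at 0.2 points is conditional on a reading that the article leaves open but does not adopt.

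**Conclusion.** The concern holds as a wrong stated figure and an unclear target, with moderate severity. On the stated inputs the minimum is 90 two-sided or 71 one-sided, and 139 overstates it by 49 or 68 participants. The result assumes exact t-test power, no allowance for dropout or multiplicity (none is stated) and d=0.30 as declared. It does not depend on how 139 arose.

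At d=0.30 the error is conservative and the planned 200 give about 99% power. Only if 0.2 points at SD 1.2 is the intended difference does the stated 80% fail: 285 or 224 would be needed, and 200 give 65% or 76% (two-sided or one-sided).

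**What to change.** Check the G*Power record to see which test and inputs produced 139. Then rewrite the Aim 3 sample-size sentences to:
- name the sidedness and a single target difference above 4.25, in points and as d;
- replace 139 with the recomputed minimum, which for d=0.30 is 90 two-sided or 71 one-sided;
- state what the planned 200 detect with 80% power: d=0.20 two-sided or 0.18 one-sided;
- take the margin of error out of the power statement and report precision separately: 95% half-width about 0.17 points at n=200 and SD 1.2.

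If the record shows that 0.2 points was the intended difference, replace the 80% claim with the power that 200 give, 65% two-sided or 76% one-sided. If an allowance such as dropout was applied, state it and show the step from the unadjusted number.

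The cost is a few sentences of wording and a look at a saved calculation. Enrolment does not change. The article reports analysis under way and results not yet published, so the correction can be made before the Aim 3 results are reported.
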